**Figure 2 Fig2:**
[figure not shown]
**Overview of dosimeter types used. (A)** Ring dosimeter. **(B)** Film dosimeter with cassette. **(C)** Eye lens thermoluminescence dosimeter. **(D)** Electronic personal dosimeter with superimposed digital display.

Two dosimeters of each type (film dosimeter, eye lens thermoluminescence dosimeter, and ring dosimeter) are placed outside the operating room and serve as reference dosimeters. All dosimeters are provided and will be evaluated by Helmholtz Zentrum München.

#### Lead protection

The surgeon, assistant surgeon, and scrub nurse wear at least a two-piece lead apron consisting of a vest (lead equivalent values of 0.70 mm Pb in the front part and 0.25 mm Pb in the back part) and a skirt reaching below the knees (lead equivalent values of 0.50 mm Pb in the front part and 0.25 mm Pb in the back part). The surgeon additionally wears a thyroid shield (lead equivalent value of 0.50 mm Pb) and lead protective goggles (lead equivalent value of 0.75 mm Pb). The anesthetist wears a one-piece lead apron (lead equivalent value of 0.35 mm Pb in the front part).

#### Surgical technique

All MIS TLIFs are performed primarily by the first author (UH) (and by RS by proxy). The patient is positioned prone on a radiolucent table, allowing fluoroscopic images in anterior-posterior and lateral projection as well as 3D scans. Prior to draping of the patient, the projections of the pedicles were identified and marked on the skin by using fluoroscopic images. The mobile 3D C-arm device, Ziehm Vision FD Vario 3D with flat panel detector (Ziehm Imaging, Nuremberg, Germany), is used for all MIS TLIFs in this study and is set on automatic exposure control with corresponding kilovolt and milliampere values of varying magnitudes; this is usual in daily practice [7]. No continuous fluoroscopy is used. Only single fluoroscopic images are acquired (C-arm in pulsed mode with 12.5 images per second).

For insertion of transpedicular Kirschner wires in the NAV group, a navigation tracker is mounted on the spinous process of one of the index vertebras via a median skin incision of approximately 2.5 cm. Subsequently, an automated 3D navigation scan is performed in apnea by using the 3D capable C-arm Ziehm Vision FD Vario 3D. During the 3D scan, the entire staff leaves the operating room and thus has a minimum distance of 6 m from the x-ray generator and patient. The 3D image set is automatically transferred to a navigation device (for example, Cart II system device; Stryker, Freiburg, Germany: SpineMap 3D navigation), and navigation tools are referenced. Via bilateral short skin incisions (2 to 3 cm), a navigated Jamshidi needle is introduced into the target vertebras through the pedicles, and Kirschner wires are inserted through the Jamshidi needle without additional use of fluoroscopic images.

In the FLUORO group, a Jamshidi needle is introduced via bilateral short skin incisions (2 to 3 cm) to locate the ideal pedicle entry point between the transverse process and lateral facet joint. This is accomplished by using tactile feedback and conventional fluoroscopic image guidance in lateral projection without exposing the anatomical structures. Then the Jamshidi needle is introduced into the target vertebras through the pedicles verified by fluoroscopic images in lateral projection when necessary, and Kirschner wires are inserted through the Jamshidi needle (Figure 3).

**Figure 3 Fig3:**
[figure not shown]
**Intraoperative view on the Kirschner wires and Jamshidi needle (orange) introduced during a minimally invasive transforaminal lumbar interbody fusion (MIS TLIF) procedure.**

Since the surgeon inserts all Kirschner wires himself, he is changing sides of the table and therefore is exposed to the corresponding scatter radiation at the ipsilateral or contralateral side of the C-arm generator, respectively. Thereafter, neurophysiological monitoring is performed for safe pedicle screw placement in both treatment groups. Integrity of the pedicle wall is evaluated with monopolar and bipolar stimulation by using a tip stimulation probe with recording of the compound muscle action potentials. With monopolar stimulation, a constant current below 7 milliampere is regarded as suspicious of pedicle perforation [8], and revising the trajectory has to be considered. Then the Kirschner wires are drawn back under fluoroscopic image guidance in lateral projection, so that their tips are positioned at the posterior border of the vertebral bodies. Their intrapedicular position is controlled by using fluoroscopic image guidance in anterior-posterior projection.

The next step is to insert and mount the non-expandable tubular retractor system METRx (Medtronic, Minneapolis, MN, USA) on the facet joint for the MIS TLIF approach. In the NAV group, the facet joint is located by using the navigated Jamshidi needle without additional use of fluoroscopic images. In the FLUORO group, the localization with the Jamshidi needle has to be performed by using fluoroscopic image guidance in lateral projection. Thereafter, in both treatment groups, the transmuscular approach is created by using METRx dilators. Finally, a METRx operation tube (diameter of 20 mm) is inserted and fixed to the table. During the following transforaminal access including facetectomy, unilateral or bilateral decompression of the spinal canal via unilateral partial hemilaminectomy, nucleotomy and implantation of the TLIF cage (with additional insertion of autologous bone into the intervertebral disc space, which has been collected during facetectomy), the surgeon uses the operating microscope from the ipsilateral side. Implantation of the cage is performed under fluoroscopic image guidance in lateral projection.

Subsequent screw insertion via the Kirschner wires and rod insertion (using CD Horizon Sextant II, CD Horizon Sextant Solera, or CD Horizon Longitude; Medtronic) is performed identically in both treatment groups without routine use of conventional fluoroscopy. If bone density is considered to be low, cement augmentation of the vertebras is performed via perforated screws under fluoroscopic image control in lateral projection [9]. Final control is made by using fluoroscopic image guidance in lateral and anterior-posterior projection.

The following guidelines must be followed as radiation protection principles: (a) continuous fluoroscopy is not used, (b) the distance between the patient’s surface and the flat panel detector is minimized, (c) beam collimation is used whenever possible, (d) a distance from the radiation source and patient’s surface (as the origin of the Compton scatter) is maintained whenever possible, (e) the hand is removed from the path of the x-ray beam when holding an instrument, and (f) no staff member stays in the operating room during acquisition of the 3D scan.

### Data collection

In this study, the primary endpoint is the radiation exposure to the surgeon during monosegmental MIS TLIFs in the FLUORO and NAV groups. The secondary endpoints are the radiation exposures to the assistant surgeon, scrub nurse, anesthetist, patient, and C-arm as well as radiation exposure in relation to the body mass index of the patient in the FLUORO and NAV groups.

### Primary endpoint measurement

Radiation exposures are determined by the applied dosimeters. Dosimeter readings are corrected with the readings of the reference dosimeters, which are positioned outside the operating room.

### Secondary endpoint measurement

Radiation exposures are determined as described above. Furthermore, radiation exposure of the EPD at the flat panel of the C-arm is read on the display at defined time points during surgery. Body mass index is obtained preoperatively and is defined as the patient’s weight in kilograms divided by the square of the height in meters.

### Ethics statement

The study protocol has been approved by the institutional ethics committee of the University of Freiburg (Germany), where the monocentric study takes place (reference number 431/12). The trial is registered with the German Clinical Trials Register (DRKS00004514) [10]. Written consent will be obtained from each participant before randomization and treatment.

### Statistical issues

#### Sample size

The estimation of the sample size is based on data provided in the literature. We determined a recruiting period of 3 years for inclusion of 40 participants with monosegmental MIS TLIF procedures.

For estimating the radiation exposure in the FLUORO group, we made the following assumptions: Bindal *et al.* [11] stated an average radiation exposure of 266 μSv to the surgeon (at the lead protected waist) during an MIS TLIF procedure using conventional fluoroscopy with an average radiation time of 101.4 seconds. A retrospective survey in our department showed an average radiation time of 55.75 seconds in 16 consecutive MIS TLIF procedures using conventional fluoroscopy. Comparing this radiation time with the data of Bindal *et al.* [11], we assume a calculated radiation exposure to the surgeon of 146.2 μSv (266 μSv × 55.75 seconds/101.4 seconds) in our department.

For estimating the radiation exposure in the NAV group, we made the following assumptions: We estimate that 12 conventional fluoroscopic images are obtained for one monosegmental MIS TLIF procedure in attendance of the surgeon (the 3D fluoroscopy-based image data set is attained in an automated fashion after the staff has left the operating room, thus not causing radiation exposure to the staff). Rampersaud *et al.* [12] stated an average radiation time of 1.1 seconds per fluoroscopic image. With this data, we assume a radiation exposure to the surgeon of 34.6 μSv (12 images × 1.1 seconds/image × 266 μSv/101.4 seconds) during a monosegmental MIS TLIF procedure using 3D fluoroscopy-based navigation.

Based on the above-mentioned assumptions, we used radiation exposures of 150 μSv (FLUORO group) and 50 μSv (NAV group) for calculation of the estimated sample size. The alpha level was set to 0.05, and the level of statistical power for calculating the sample size was set to 0.8. This power analysis led to a sample size of n = 17 for each group for monosegmental MIS TLIF procedures applying the two-tailed *t* test for independent samples. We aim to include 20 patients with monosegmental MIS TLIF procedures in each group.

#### Statistical analysis

The primary endpoint (radiation exposure to the surgeon) will be tested at the 0.05 level. Results will be expressed as means with standard deviations. Analysis of independent continuous quantitative variables between groups will be performed by using the two-tailed Student’s *t* test. Pearson’s correlation test will be used to determine correlations between two variables. Statistical comparisons for categorical values between groups will be performed by using the two-tailed Fisher exact test. Prism 6 for Mac (GraphPad Software Inc., La Jolla, CA, USA) will be used as statistical software.

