### Study treatments

#### Dosimeter setup

Dosimeters are attached to the surgeon, assistant surgeon, scrub nurse, anesthetist, patient, and C-arm in the operating room (Table 2). Four different types of dosimeters are used (Figure 2). Film dosimeters (AWST-FILM GD 60, *H*_p_(10); Helmholtz Zentrum München, part of the German Research Center for Environmental Health, Personal Monitoring Service, Munich, Germany) are attached to the trunk of the surgeon, assistant surgeon, scrub nurse, anesthetist, patient, and C-arm. Eye lens thermoluminescence dosimeters (EYE-D, *H*_p_(3); Radcard, Krakow, Poland) are attached to the surgeon, assistant surgeon, and scrub nurse. Ring dosimeters (AWST-TL-TD 60, type W; Helmholtz Zentrum München) are tightened around the ring fingers of the surgeon. Moreover, an Electronic Personal Dosimeter (EPD Mk2, *H*_p_(10) mode; Thermo Scientific, Schwerte, Germany) is installed at the flat panel detector of the C-arm to read radiation exposures at predetermined time points during surgery. This dosimeter location approximately corresponds to a surgeon who does not step back from the radiation source when applying x-rays, and this is regularly the case in most operating rooms. With the EPD, we have radiation exposure readings at any time of the operation and thus have the possibility to approximately relate radiation exposures to certain steps of the operation.

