**Table 2 Tab2:** **Survey of the intraoperative dosimeter setup**

	**Location**	**Dosimeter type**	**Dosimeter lead protected?**
Surgeon	Left ring finger	Ring dosimeter	Unprotected
	Right ring finger	Ring dosimeter	Unprotected
	Middle forehead	Eye lens dosimeter	Unprotected
	Under lead goggles (left glass)	Eye lens dosimeter	Protected
	Thyroid gland, above lead shield	Film dosimeter	Unprotected
	Thyroid gland, under lead shield	Film dosimeter	Protected
	Left chest, above lead apron	Film dosimeter	Unprotected
	Left chest, under lead apron	Film dosimeter	Protected
	Gonad, under lead apron	Film dosimeter	Protected
	Right knee, under lead apron	Film dosimeter	Protected
	Back, between shoulder blades, above lead apron	Film dosimeter	Unprotected
Assistant surgeon	Middle forehead	Eye lens dosimeter	Unprotected
	Left chest, above lead apron	Film dosimeter	Unprotected
	Left chest, under lead apron	Film dosimeter	Protected
Scrub nurse	Middle forehead	Eye lens dosimeter	Unprotected
	Left chest, above lead apron	Film dosimeter	Unprotected
	Left chest, under lead apron	Film dosimeter	Protected
Anesthetist	Left chest, above lead apron	Film dosimeter	Unprotected
	Left chest, under lead apron	Film dosimeter	Protected
Patient	Thyroid gland	Film dosimeter	Unprotected
	Chest	Film dosimeter	Unprotected
	Gonad	Film dosimeter	Unprotected
C-arm	Next to generator	EPD	Unprotected
	Next to generator	Film dosimeter^a^	Unprotected
	Next to flat panel detector	Film dosimeter^a^	Unprotected

^a^Film dosimeters on the C-arm are removed during the three-dimensional (3D) scan (NAV group, three-dimensional fluoroscopy-based navigation group) since the staff is outside the operating room during the 3D scan. EPD, electronic personal dosimeter.

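### The primary endpoint, surgeon radiation exposure, is not tied to one variable: the surgeon wears 11 dosimeters, none is named as primary, and the planning dose comes from a site not among them

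*Protocol article*

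**What the plan says.** Under Data collection, the protocol article states that "the primary endpoint is the radiation exposure to the surgeon during monosegmental MIS TLIFs in the FLUORO and NAV groups". The section on primary endpoint measurement adds "Radiation exposures are determined by the applied dosimeters" and a correction by reference dosimeters kept outside the operating room. Under Statistical analysis: "The primary endpoint (radiation exposure to the surgeon) will be tested at the 0.05 level". The same section gives the test: "Analysis of independent continuous quantitative variables between groups will be performed by using the two-tailed" Student's t test.

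Table 2 lists these dosimeters for the surgeon:

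- **Ring (2):** left and right ring finger, both unprotected. The text confirms that these "are tightened around the ring fingers of the surgeon".
- **Eye lens (2):** middle forehead, unprotected; and "Under lead goggles (left glass"), protected.
- **Film (7):** thyroid above and under the shield, left chest above and under the apron, gonad under the apron, right knee under the apron, and "Back, between shoulder blades, above lead apron".

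The Sample size section starts from a published average of 266 μSv "to the surgeon (at the lead protected waist) during an MIS TLIF procedure using conventional fluoroscopy". It scales this to local radiation times, rounds to 150 μSv (FLUORO) and 50 μSv (NAV), and arrives at 17 per group, with 20 planned.

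**The concern.** A primary endpoint should point to one number per operation. Here it points to a person who wears 11 instruments, and the section headed as the primary endpoint measurement does not choose among them or say how to combine them.

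Three things are at stake. First, the 0.05 level protects the claim only if the variable is fixed before the readings are compared. A site picked afterwards, or a claim based on whichever site is significant, inflates the error even if only one test is reported. Second, a mixed result, such as a difference at the chest but not at the eye lens, has no defined conclusion. Third, the planning means belong to a waist dose under lead, so it is unclear which measured variable the trial is powered for.

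**Working it through.** **1. The plan's own planning figures.**
- FLUORO: 266 × 55.75 / 101.4 = 146.2 μSv, as stated, rounded to 150.
- NAV: 12 × 1.1 × 266 / 101.4 = 34.6 μSv, as stated, with 50 used.
- Difference used: 150 − 50 = 100 μSv.
- The stated 17 per group (two-sided t test, alpha 0.05, power 0.80) cannot be reproduced from the article alone, because it gives no SD. With an assumed SD of 100 μSv the exact t-test calculation gives 16.7, rounded up to 17; any SD from about 97.7 to 100.9 μSv also gives 17. At 20 per group and SD 100 the power is about 87%. The missing SD is a separate matter, and the SD is used below only to price one alternative.

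**2. Count of candidate variables (Table 2, surgeon rows).**
- By type: 2 ring + 2 eye lens + 7 film = 11.
- Unprotected: 2 ring, forehead, thyroid above shield, chest above apron, back = 6.
- Protected: under goggles, thyroid under shield, chest under apron, gonad, knee = 5.
- Waist: 0.

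**3. Does the text supply a default?**
- *All 11 combined:* no such rule is stated. The Dosimeter setup section gives Hp(10) for film and Hp(3) for eye lens, with ring a third type, so a total would mix dose quantities and add shielded to unshielded sites.
- *The planning site:* the waist is not in Table 2. Gonad under the apron and left chest under the apron are both protected trunk sites, and nothing chooses between them.

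**4. Size of the problem if all 11 were tested at 0.05.**
Under independence: 1 − (1 − 0.05)^11 = 1 − 0.95^11 = 0.431.

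The documents give no correlation between sites, so a range is assumed. Simulation: 40,000 trials per row, 20 per group, 11 equally correlated normal readings, no true difference, each reading tested by a two-sided t test at 0.05.

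| Assumed pairwise correlation | Chance of at least one false positive |
|---|---|
| 0 | 43% |
| 0.5 | 31% |
| 0.7 | 23% |
| 0.8 | 18% |
| 0.9 | 13% |
| 0.95 | 10% |
| 1.0 | 5% |

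**5. Price of keeping all 11 with control.**
Bonferroni: 0.05 / 11 = 0.00455 per test. With the assumed difference of 100 and SD of 100 μSv, 80% power on a given dosimeter needs 29.1, so 30 per group. The planned 20 per group gives about 56%.

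**The case against.** A reader might infer that the trial plans 11 primary tests and will count any significant one as success. The documents do not support that. Both the Data collection and Statistical analysis sections speak of a single primary endpoint, and no sentence says that each dosimeter is tested as primary. The false-positive figures therefore describe what the wording permits, not what is announced.

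A reader might also take 43% as the expected error rate. All 11 readings come from the same surgeon position, source and operation, and several are paired above and below one shield, so strong positive correlation is likely and the lower rows of the table are more realistic. The table also counts false positives in either direction. A false claim favouring NAV occurs in roughly 9%, 7% and 5% of trials at correlations of 0.8, 0.9 and 0.95, against a nominal 2.5%. That is much less than 43%, but still about two to four times nominal.

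A third tempting reading is that the sample size rests on a site unrelated to anything measured. That goes too far: the waist dose is a literature proxy, and two nearby shielded trunk sites are measured. What remains is that the protocol does not link the proxy to either of them.

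Nor is every summary ruled out. The seven film dosimeters share one dose quantity, so a summary of film sites with the same shielding would be coherent.

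Finally, this is a condensed article, and multiplicity rules may properly sit in a full protocol or analysis plan. The absence of such a rule is not the point here. The article devotes a section to measuring the primary endpoint and a full table to the dosimeters, and what it fixes there does not identify one variable.

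**Conclusion.** The point holds as a badly fixed primary variable. The count of 11, the absence of a named site or summary, and the absence of a waist dosimeter are facts of the text and need no assumption.

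The size is conditional. If all 11 sites were tested at 0.05, the chance of at least one false positive would be about 10% to 31% for assumed correlations of 0.95 to 0.5 (18% at 0.8), with 43% as the independence case, against the stated 5%. These figures assume equal correlations, normal readings and 20 per group. Only perfect correlation would bring the rate back to 5%. Since this is the trial's only confirmatory claim, it should be settled before readings are compared by group.

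**What to change.** By dated amendment, before any comparison of readings by group, revise the Data collection, Primary endpoint measurement and Statistical analysis sections to:

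1. Name one surgeon dosimeter from Table 2, or one pre-defined summary of dosimeters of the same type and shielding, as the primary variable for monosegmental procedures.
2. Test only that variable at 0.05.
3. Report the remaining surgeon sites as secondary.
4. State in the Sample size section how the planning dose relates to the chosen variable.

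The choice is the sponsor's. A shielded trunk site, for example left chest or gonad under the apron, keeps the waist-based planning dose closest to what is measured. If an unshielded site is chosen, the planning means and SD must be restated for it and the sample size checked again, because the article gives no dose for any unshielded site.

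Cost: a few sentences and no extra measurements. With a shielded trunk site and the present planning assumptions, no extra patients are needed. The downside is that claims at the other sites become supportive only.

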## Discussion

Since there is no threshold dose according to the stochastic model for radiation injuries, spine surgeons should apply x-rays thoughtfully and sparingly [13,14]. Minimally invasive fusion techniques, in particular, can result in increased x-ray exposure times [3]. Bearing in mind that surgeon and staff are exposed to radiation during their daily routine, one has to find solutions to reduce the occupational radiation exposure. Radiation protection principles like wearing adequate lead equipment (including thyroid shield and lead glass goggles), application of beam collimation, and keeping a distance from the radiation source should be self-evident [7]. Further reduction might be obtained by using 3D fluoroscopy-based navigation since the staff is leaving the operating room for acquisition of the 3D image scan, thus avoiding additional radiation exposure. In contrast, application of 3D fluoroscopy-based navigation might increase radiation exposure to the patient. This randomized study aims to compare the radiation exposure to the operating staff and patient during MIS TLIF procedures using conventional fluoroscopy or 3D fluoroscopy-based navigation.

## Trial status

This trial is currently recruiting participants. Enrollment is expected to be finished in 2016.

## Abbreviations

2D: Two-dimensional
3D: Three-dimensional
EPD: Electronic personal dosimeter
FLUORO group: Conventional fluoroscopy group
MIS TLIF: Minimally invasive transforaminal lumbar interbody fusion
NAV group: Three-dimensional fluoroscopy-based navigation group
Pb: Lead
TLIF: Transforaminal lumbar interbody fusion
